## Abstract

**Background:**

Hypoxic-ischaemic encephalopathy is associated with development of cerebral palsy and cognitive disability later in life and is therefore one of the fundamental problems in perinatal medicine. The xanthine-oxidase inhibitor allopurinol reduces the formation of free radicals, thereby limiting the amount of hypoxia-reperfusion damage. In case of suspected intra-uterine hypoxia, both animal and human studies suggest that maternal administration of allopurinol immediately prior to delivery reduces hypoxic-ischaemic encephalopathy.

**Methods/Design:**

The proposed trial is a randomized double blind placebo controlled multicenter study in pregnant women at term in whom the foetus is suspected of intra-uterine hypoxia.

Allopurinol 500 mg IV or placebo will be administered antenatally to the pregnant woman when foetal hypoxia is suspected. Foetal distress is being diagnosed by the clinician as an abnormal or non-reassuring foetal heart rate trace, preferably accompanied by either significant ST-wave abnormalities (as detected by the STAN-monitor) or an abnormal foetal blood scalp sampling (pH < 7.20).

Primary outcome measures are the amount of S100B (a marker for brain tissue damage) and the severity of oxidative stress (measured by isoprostane, neuroprostane, non protein bound iron and hypoxanthine), both measured in umbilical cord blood. Secondary outcome measures are neonatal mortality, serious composite neonatal morbidity and long-term neurological outcome. Furthermore pharmacokinetics and pharmacodynamics will be investigated.

We expect an inclusion of 220 patients (110 per group) to be feasible in an inclusion period of two years. Given a suspected mean value of S100B of 1.05 ug/L (SD 0.37 ug/L) in the placebo group this trial has a power of 90% (alpha 0.05) to detect a mean value of S100B of 0.89 ug/L (SD 0.37 ug/L) in the 'allopurinol-treated' group (z-test_2-sided_). Analysis will be by intention to treat and it allows for one interim analysis.

**Discussion:**

In this trial we aim to answer the question whether antenatal allopurinol administration reduces hypoxic-ischaemic encephalopathy in neonates exposed to foetal hypoxia.

**Trial registration number:**

Clinical Trials, protocol registration system: NCT00189007

## Background

Hypoxic-ischaemic encephalopathy is associated with development of cerebral palsy and cognitive disability later in life [1]. The recognition, prevention and treatment of intra-uterine hypoxia is therefore one of the main priorities in perinatal medicine. Animal and human studies have shown that brain damage not only occurs during the hypoxic-ischaemic event, but continues for hours up to days upon and after reoxygenation and reperfusion and is caused by production of free radicals [2].

Free radical formation due to conversion of hypoxanthine into xanthine by xanthine-oxidase is very important during this process [3]. Administration of the xanthine-oxidase inhibitor allopurinol (ALLO) reduces the production of free radicals, thereby limiting the amount of hypoxia-reperfusion damage [4,5]. Furthermore, ALLO also has a non-protein bound iron (pro-radical) chelating and direct free radical (hydroxyl) scavenging effect. Animal research in asphyxiated pigs demonstrated beneficial effects of postnatally administrated ALLO on cerebral energy status and cytotoxic oedema [6].

A prospective randomized study in human neonates, examining the effects of ALLO in term asphyxiated neonates, showed an improvement of electrocortical brain activity and a reduction in free radical formation after neonatal ALLO administration [7]. A more recent paper by Gunes et al [8] reports an improved neurological outcome after postnatal ALLO administration compared to a placebo in term asphyxiated neonates. Benders et al however demonstrated that ALLO was not effective if administrated 3 to 4 hours after the hypoxic incident to severely asphyxiated neonates [9]. However, when the most severely asphyxiated children were excluded from the study, a beneficial effect of ALLO was seen on neurological development. This is in line with previous studies by Gluckman et al on neonatal head cooling [10]. They also demonstrated a beneficial effect of their treatment after exclusion of the most severely asphyxiated neonates. Apparently, no advantage of neonatal treatment is seen anymore, when the interval to the initiation of treatment is too long or when the brain damage is too severe. This has probably been the major disadvantage of late post neonatal treatment with ALLO on the Neonatal Intensive Care Unit (NICU). ALLO administrated at the NICU is likely to be given too late to provide adequate neuroprotection during the early period of reoxygenation in which the vast amount of free radicals is being produced.

Apparently, when the asphyxia has been too severe, the inflicted brain damage can no longer be reversed. It is conceivable that earlier ALLO treatment, i.e. the use of ALLO during labour in case of suspected foetal hypoxia, provides the opportunity to start earlier with the treatment, thereby limiting the amount of hypoxia-reperfusion injury and improving neurological outcome.

Pharmacological data have been published by Boda et al, who showed that pharmacological plasma levels were reached in the human foetus after ALLO administration to the mother [11]. A systematic review in Pubmed, searching for [allopurinol, foetus, neonate, asphyxia, hypoxia] did not provide us with any additional studies performed in humans. Some animal studies have been performed using piglets (neonatal administration), sheep and sows (maternal administration) [6,12-14]. These studies showed improved outcome after allopurinol treatment on cerebral energy status and recovery of umbilical blood flow respectively.

We recently performed a prospective randomized placebo controlled pilot study, in which we administered ALLO to the pregnant woman when foetal asphyxia was imminent. Data from this pilot study show an inverse correlation between levels of ALLO and the amount of S100B, a biomarker for brain tissue damage, in cord blood [15]. In addition, we performed a study in the chronically instrumented foetal sheep, in which we showed evidence of cardio- and neuroprotection after antenatal ALLO administration to the pregnant ewe during repeated periods of ischaemia [13,16].

### Incidence and financial impact of birth asphyxia

Birth asphyxia carries a high incidence, 4-9 per 1000 live born neonates. On estimate 1-4 of these neonates will die or develop a severe handicap [17,18]. With almost 200.000 deliveries in the Netherlands annually, this implicates that each year approximately 800 neonates will die or suffer from a handicap due to birth asphyxia. Moreover, there is evidence that individuals suffering from moderate birth asphyxia, develop behavioural problems later in life [19].

The health care costs of asphyxia are enormous. Many of these children are admitted to a neonatal intensive care unit at a cost of € 1.500, - per day, with an average duration of admission of 10 days. Estimated costs of disabled children are € 80.000, - and € 20.000, - yearly for severely and moderately handicapped children respectively. The costs of neonatal care are annually 20 million Euros, whereas the costs of care for disabled children born in one year are more than one hundred million Euros.

As the costs of ALLO and its administration are relatively low (100 Euros per pregnant woman), a small treatment effect will already make the intervention cost-effective.

### Safety of allopurinol

Allopurinol has been used in internal medicine for many years for the treatment of gout. Side effects of ALLO are rare and most commonly include symptoms of hypersensitivity like skin rashes [20]. Stevens-Johnson syndrome has been reported, but only after prolonged treatment (> 10 days) in case of gout [21]. During previously performed studies in pregnant women and neonates, no adverse reactions were seen [11,15,22,23].

## Methods/Design

### Aims

The objective of the study is to test the hypothesis that intra-uterine treatment with ALLO in case of suspected foetal hypoxia will reduce brain damage and with that may improve neonatal outcome.

### Participants/eligibility criteria

Pregnant women with a gestational age of at least 36 weeks and suspected intra-uterine hypoxia (foetal distress) during labour can be included in the trial. Foetal distress is being diagnosed by the clinician as an abnormal or non-reassuring foetal heart rate trace, preferably accompanied by either significant ST-wave abnormalities (as detected by the STAN-monitor) or an abnormal foetal blood scalp sampling (pH < 7.20). Neonates suspected of chromosomal or congenital anomalies will be excluded.

### Procedures, recruitment, randomization and collection of baseline data

The study will be a randomized double blind placebo controlled multicenter study. Hospitals which participate in the Dutch Consortium for Studies in Women's health and reproductivity will participate in the trial. The study will be staffed by research midwives and -nurses, who will counsel patients at the outpatient clinic or at the obstetric ward.

Before entry into the study, subjects will be informed about the aims, methods, reasonably anticipated benefits and potential hazards of the study. Subjects will be informed that their participation is voluntary and that they may withdraw consent to participate at any time during the study. They will be informed that choosing not to participate will not affect their care. In every center an independent gynaecologist will be available for more detailed information both for patients and colleagues if required. After giving sufficient information, written informed consent will be obtained. The consent form must be signed before performance of any study-related activity.

In case of suspected foetal distress and written informed consent, the patient will be randomized immediately prior to delivery (Figure 1).

**Figure 1 F1:**
[figure not shown]
**Flowchart ALLO-trial**.

All details of delivery are recorded in the case record form that is accessible through a website http://www.studies-obsgyn.nl/allo. In case of admittance of one or more children to the neonatal intensive care unit, details of this admittance are also recorded.

Data will be collected using Oracle Clinical Remote Data Capture (RDC), which is a new generation of application systems that enable collection and cleanup of clinical trial data using the Internet. For detailed information on Oracle RDC see http://www.ctc-g.co.jp/~CTCLS/opa/en/. The expertise for this technology is already used in the study group and applied in the ZonMw funded consortium studies that are currently running.

### Interventions

All women who are identified as having suspected foetal distress and have given informed consent prior to delivery will be randomized in two groups:

One group of pregnant women will receive one IV dosage of 500 mg ALLO. The other group will receive one IV dosage of placebo antenatally.

### Outcome measures

Primary outcome measures are related to biochemical brain damage markers (S100B, enolase) and the severity of oxidative stress as measured by isoprostane, neuroprostane, non protein bound iron and hypoxanthine in umbilical cord blood.

The main primary outcome measure will be the protein S100B as this is, at present, the most validated biochemical marker for brain tissue damage.

Secondary outcome parameters are neonatal mortality and short term neonatal morbidity, such as hypoglycaemia, convulsions and post-hypoxic neonatal encephalopathy, length of admission at the neonatal intensive care unit and placental transfer, pharmacodynamics and -kinetics of ALLO. Neonatal encephalopathy will be assessed by Sarnat- and Thompson scores [24,25].

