### Follow up of women and infants

Blood sampling will be performed to assess the amount of tissue damage (i.e. S100B, enolase, troponin), oxidative stress (i.e hypoxanthine, isoprostane, neuroprostane and non protein bound iron) and ALLO plasma levels. Immediately after delivery, samples of cord blood and maternal blood are obtained. One hour and 18-24 hours after birth neonatal blood samples are obtained in all children with clinically indicated blood sampling.

Long-term follow-up using neuropsychological tests and validated neurodevelopmental questionnaires at the age of 4-5 and 8 years and additional MRI at the age of 8 years is desirable, but is depending on future funding.

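### Hypoxanthine is a primary marker of oxidative stress, yet it is the substrate of the enzyme that allopurinol blocks, so its between-arm difference cannot be separated from drug action

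*Protocol article*

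**What the plan says.** The Abstract (Methods/Design) gives as the second part of the primary outcome "the severity of oxidative stress (measured by isoprostane, neuroprostane, non protein bound iron and hypoxanthine), both measured in umbilical cord blood". The Outcome measures section repeats this: "the severity of oxidative stress as measured by isoprostane, neuroprostane, non protein bound iron and hypoxanthine in umbilical cord blood". The section on follow up of women and infants again groups hypoxanthine with the oxidative-stress assays. Outcome measures names S100B as the main one among the primary outcomes. It also lists the pharmacodynamics of allopurinol among the secondary outcomes, without assigning hypoxanthine to them.

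The Background section sets out the mechanism: "Free radical formation due to conversion of hypoxanthine into xanthine by xanthine-oxidase is very important during this process". It continues: "Administration of the xanthine-oxidase inhibitor allopurinol (ALLO) reduces the production of free radicals, thereby limiting the amount of hypoxia-reperfusion damage". It adds that "ALLO also has a non-protein bound iron (pro-radical) chelating and direct free radical (hydroxyl) scavenging effect".

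On exposure at the time of sampling, Interventions states "One group of pregnant women will receive one IV dosage of 500 mg ALLO", given antenatally. Background cites a report that "pharmacological plasma levels were reached in the human foetus after ALLO administration to the mother". The follow-up section states "Immediately after delivery, samples of cord blood and maternal blood are obtained".

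The article gives no expected direction for hypoxanthine and does not say how a higher value in the allopurinol arm would be read.

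**The concern.** To compare the severity of oxidative stress between arms, a marker should relate to oxidative stress in the same way in both. On the article's own account hypoxanthine does not. It lies upstream of the step that the drug blocks. Under placebo, more hypoxanthine can plausibly be read as more hypoxia and more material for radical formation. Under allopurinol, more hypoxanthine may only show that the enzyme is inhibited.

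At stake is what may be concluded from one of the primary measures. A higher level under allopurinol, read under the label the article gives it, would look like more oxidative stress when it may be a sign that the drug is working. It could also appear to contradict favourable isoprostane or neuroprostane results. A null result would be equally hard to read, because a real benefit and enzyme blockade can cancel.

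**Working it through.** **Figures available.** The article's only power figure concerns S100B: 110 per arm, means 1.05 and 0.89 ug/L, SD 0.37, two-sided alpha 0.05, stated power 90%. It reproduces. The standardised difference is 0.16/0.37 = 0.432, its standard error is √(2/110) = 0.135, and the power is Φ(0.432/0.135 − 1.96) = 89.4%. No mean, SD or expected effect is given for hypoxanthine, so there is no hypoxanthine figure to reproduce. The check is one of reasoning.

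**The texts side by side.**
1. Role: a primary measure of how severe oxidative stress is (Abstract, Outcome measures).
2. Biology: radicals form as xanthine-oxidase turns hypoxanthine into xanthine (Background).
3. Drug: allopurinol inhibits that enzyme (Background).
4. Timing: the drug is given before delivery and cord blood is drawn immediately after (Interventions; Follow up of women and infants). Foetal exposure after maternal dosing is cited in Background.

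From 2 to 4, the marker is sampled while its own removal may be altered in one arm only. The relation assumed in 1 then need not be the same in the two arms.

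**Illustration of the sign.** Assume, for this purpose only, a steady state in which level = production / clearance. Let allopurinol cut total clearance by a fraction f and, through real benefit, cut hypoxanthine production by a fraction g. Then

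ratio (allopurinol / placebo) = (1 − g) / (1 − f).

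| Clearance cut f | Production unchanged (g = 0) | Production cut 20% (g = 0.20) |
|---|---|---|
| 10% | 1/0.90 = 1.11 | 0.80/0.90 = 0.89 |
| 30% | 1/0.70 = 1.43 | 0.80/0.70 = 1.14 |
| 50% | 1/0.50 = 2.00 | 0.80/0.50 = 1.60 |

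All values of f and g are assumed; none comes from the article. The same 20% fall in production shows as a lower level when f is 10%, no difference when f is 20% (0.80/0.80 = 1.00), and a higher level when f is 30%. Even where the sign is right, the fall is understated (0.89 against 0.80).

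**Can the level rise while radical formation falls?** Suppose the enzyme accounts for a share s of total clearance and the drug cuts its activity by a fraction x, with production unchanged, so that f = sx. The level changes by 1/(1 − sx), which is above 1. Turnover through the enzyme changes by (1 − x)/(1 − sx), which is below 1 whenever s is below 1. The two then move in opposite directions. This needs either another route of removal or a sample taken before a new steady state is reached. The article specifies neither, but it does state that the drug lowers radical production.

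**The case against.** The strongest case against has four parts.

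- **The main conclusion is protected.** S100B is the main primary outcome, the sample size rests on it alone, and the interim analysis is not tied to hypoxanthine. This stands. A reader might infer that the trial's main test is compromised; it is not.
- **No misreading is written down.** The article gives no decision rule for hypoxanthine, and its authors describe the pathway themselves, so they may well interpret a rise correctly. This stands in part: it cannot be said that harm would be reported. It does not remove the point, because the role that the article does fix, a primary measure of severity, conflicts with the mechanism it describes. That is a stated choice and not a detail left to a fuller document.
- **Size and sign are unknown.** Randomisation is shortly before delivery. The interval from dose to sample and the degree of foetal enzyme inhibition are not given, and less hypoxia could itself lower hypoxanthine. This stands. The supportable claim is that the difference cannot be separated from drug action, not that it is nothing but drug action or must point the wrong way.
- **Acting on a marker is not bias in itself.** This stands for non protein bound iron. A reader might extend the concern to it because Background says the drug chelates it. The same sentence calls this iron pro-radical, so a lower level lies on the intended causal path and points the right way. The affected count is one of four, not two of four.

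It is also tempting to say that a purely pharmacological shift of about 0.43 SD would be declared significant about 90% of the time. That is the detectable effect for any continuous, approximately normal marker with 110 per arm, taken here from the S100B inputs. It is not evidence that allopurinol moves hypoxanthine by that or any amount.

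**Conclusion.** The point holds in limited form. Hypoxanthine is given a primary role as a measure of oxidative-stress severity although, by the article's own account, it is the substrate of the enzyme the drug inhibits. Its between-arm difference cannot be attributed to oxidative stress apart from direct drug action, and it may be higher under allopurinol while radical formation is lower.

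The reach is one of the four oxidative-stress markers. The net size and direction cannot be computed from the article, and the ratios above only show that the sign depends on assumptions. The conclusion rests on the mechanism in Background and on active drug being present in the foetus when cord blood is drawn. The article supports the latter by citation but does not quantify it. S100B, its sample size, and the isoprostane, neuroprostane and iron measures are not affected.

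**What to change.** Take hypoxanthine out of the primary oxidative-stress measures and list it with the pharmacodynamic outcomes that Outcome measures already contains, with matching changes in the Abstract and the follow-up section. State in advance that a higher value under allopurinol will not be taken as evidence of more oxidative stress. Keep isoprostane, neuroprostane and non protein bound iron as the oxidative-stress measures. Make the change before any between-arm hypoxanthine results are seen.

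The cost is one fewer marker under the oxidative-stress heading. Sampling, assays and sample size stay as they are.

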### Follow up of women and infants

Blood sampling will be performed to assess the amount of tissue damage (i.e. S100B, enolase, troponin), oxidative stress (i.e hypoxanthine, isoprostane, neuroprostane and non protein bound iron) and ALLO plasma levels. Immediately after delivery, samples of cord blood and maternal blood are obtained. One hour and 18-24 hours after birth neonatal blood samples are obtained in all children with clinically indicated blood sampling.

Long-term follow-up using neuropsychological tests and validated neurodevelopmental questionnaires at the age of 4-5 and 8 years and additional MRI at the age of 8 years is desirable, but is depending on future funding.

### Statistical issues

#### Sample size

The sample size is calculated based on the primary outcome measure cord-S100B as a marker of brain damage. Our own pilot study showed a mean value of S100B of 1.05 ug/L (SD 0.37 ug/L) in the 'non-treated' group with suspected intra-uterine hypoxia. Based on this same pilot study we expect the mean value of S100B to be lower in the 'allopurinol-treated' group compared to the 'non-treated group'.

Based on the accrual of patients in our pilot study we consider an inclusion of 220 patients (110 ALLO, 110 placebo) to be feasible in an inclusion period of 2 years. Given a suspected mean value of S100B of 1.05 ug/L (SD 0.37 ug/L) in the placebo group this trial has a power of 90% with an alpha of 0.05 to detect a mean value of S100B of 0.89 ug/L (SD 0.37 ug/L) in the 'allopurinol-treated' group (z-test_2-sided_)[15].

#### Data analysis

Data will be analyzed according to the intention to treat principle. Outcome measures will be analyzed with (non)parametric tests where continuous variables are concerned. Proportional data will be reported as relative risks with 95% confidence intervals. Multivariable regression techniques will be applied to correct for any important differences in prognostic baseline characteristics, despite of randomization, by adding all prognostic variables as independent variables. Both corrected and uncorrected group differences will be reported. Numbers needed to treat (NNT) will be reported for both continuous and discrete data.

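### Covariate adjustment of S100B depends on baseline imbalance seen after randomisation, and neither the adjusted nor the unadjusted result is named as primary; the planned power holds, but precision is forgone

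*Protocol article*

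**What the plan says.** The Data analysis section of the protocol article sets a rule for covariates: "Multivariable regression techniques will be applied to correct for any important differences in prognostic baseline characteristics, despite of randomization, by adding all prognostic variables". The next sentence adds: "Both corrected and uncorrected group differences will be reported". For continuous outcomes it says: "Outcome measures will be analyzed with (non)parametric tests where continuous variables are concerned". Nothing in the section says which result decides the S100B question.

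The Sample size section is more definite about the endpoint and the test: "The sample size is calculated based on the primary outcome measure cord-S100B as a marker of brain damage". The calculation is an unadjusted two-sided z-test of mean S100B with 110 women per arm, and it states that "this trial has a power of 90% with an alpha of 0.05". The total of 220 is justified by what can be recruited in two years.

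The Interim analysis section plans one look after 110 women, using an O'Brien-Fleming type spending function.

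**The concern.** In a randomised trial, baseline imbalance is due to chance. The reason to adjust is that a variable predicts the outcome, and that can be judged before any data are seen. A rule triggered by observed imbalance adjusts in some trials and not in others. It therefore misses most of the precision that the same covariates would give if they were always used.

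Reporting two estimates without ranking them leaves it open which one answers the primary question. It also leaves open which statistic is compared with the interim boundary. Because the model depends on observed imbalance, it could differ between the interim and final analyses.

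What is at stake is a clearly defined S100B result, and precision that needs no extra recruitment in a trial whose size was set by feasibility.

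**Working it through.** **Inputs from the Sample size section.** Means 1.05 and 0.89 µg/L, so the difference is 1.05 − 0.89 = 0.16; SD 0.37 in both arms; 110 per arm; two-sided alpha 0.05.

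**Assumptions, because the document gives none.** The share of S100B variance explained by baseline covariates (R²), the number of covariates, and the size of imbalance that triggers adjustment.

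**Step 1: reproduce the stated power.**
- Standard error = 0.37 × √(2/110) = 0.0499.
- Expected z = 0.16 / 0.0499 = 3.207.
- Power = Φ(3.207 − 1.960) = Φ(1.247) = 89.4%.
- For exactly 90% power the formula needs 113 per arm, against 110 stated.

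The plan's 90% is confirmed for the unadjusted test.

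**Step 2: adjustment fixed in advance.** The residual SD becomes 0.37 × √(1 − R²), so the expected z becomes 3.207 / √(1 − R²).
- R² = 0.1: z = 3.381, power 92.2%, equivalent to 102 per arm for 90% power.
- R² = 0.2: z = 3.586, power 94.8%, equivalent to 90 per arm.
- R² = 0.3: z = 3.833, power 96.9%, equivalent to 79 per arm.

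**Step 3: the imbalance-triggered rule.** Assume three independent covariates and a trigger of p < 0.10 on any of them. The chance that adjustment happens at all is 1 − 0.9³ = 27%. In the other 73% of trials the unadjusted test stands, so most of the gain in step 2 is not realised.

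The text can be read as adding only the imbalanced covariates or, more literally, as adding all of them once triggered. Simulation with 110 per arm gives:

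| R² | Type I error, triggered (imbalanced only / all) | Power, unadjusted | Power, triggered (imbalanced only / all) | Power, fixed adjustment |
|---|---|---|---|---|
| 0.1 | 4.5% / 5% | 89% | 90% / 90% | 92% |
| 0.2 | 4.2% / 4% | 89% | 90% / 91% | 94% |
| 0.3 | 3.9% / 4% | 89% | 91% / 92% | 96% |

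The simulated fixed-adjustment power agrees with the formula in step 2 to within about a point.

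**Step 4: sensitivity to the assumptions.** With five covariates and a trigger of |z| > 1.96, normal data give triggered power (imbalanced only / all) of 89.4% / 89.7% at R² = 0.1 and 90.3% / 91.7% at R² = 0.3. Fixed adjustment gives 91.9% and 96.8%. Type I error of the triggered rule stays between 3.7% and 4.7% for R² up to 0.5, with normal or log-normal data. Simulation error in this set is about 0.25 points for type I error and 0.5 points for power.

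**Step 5: if the better of the two reported results were claimed.** Type I error is 6.5%, 7.1% and 7.6% for R² = 0.1, 0.2 and 0.3 in the three-covariate setting. It is 6.3% to 8.7% in the five-covariate setting with R² up to 0.5. This step adds a selection that the document does not state.

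None of these figures allows for the interim look.

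**The case against.** The strongest reply is that the protocol already points to one analysis. S100B is named as the main primary outcome, and the trial is sized on an unadjusted comparison of means, so the unadjusted result is the natural primary one. Committing to publish both estimates limits selective reporting. The covariate list and the rule for choosing a parametric or rank test are details that an article may leave to an analysis plan that is not shown.

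Much of this stands. Reporting both estimates is good practice. The absence of a covariate list and the open choice of test are not findings in themselves. The sizing test does suggest an unadjusted primary analysis, though the Data analysis section never confirms it. What the reply does not remove is the trigger. The article states it as a rule, and an analysis plan that followed the rule would carry it forward.

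Three stronger readings are tempting, and the documents do not support them:
- **Power falls below plan.** It does not. The stated 90% belongs to the unadjusted test and reproduces at 89.4%, and the triggered rule is at or slightly above that. What is missed is a gain.
- **The planned procedure inflates type I error.** It does not. The triggered rule is mildly conservative; inflation needs a choice of the favourable result.
- **Post-randomisation variables such as mode of delivery could enter the model.** The sentence is limited to baseline characteristics, and the reference to all prognostic variables is most naturally read within that limit.

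A reader could also take the reference to all prognostic variables to mean a full set that is always used. The wording about differences arising despite randomisation makes the triggered reading more natural, and the ambiguity is itself a reason to reword.

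**Conclusion.** The point holds as a matter of efficiency and clarity. It does not invalidate the design. The article ties adjustment of S100B to observed imbalance and ranks neither estimate.

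For R² of 0.1 to 0.3, fixed adjustment would raise power to about 92% to 97%, against about 90% to 92% under the rule as written. That is a gain forgone of roughly 2 to 6 points. Type I error under the rule as written is about 4% to 5%; the 6.5% to 8% figure applies only if the better of the two results is claimed.

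The direction is the same under both sets of assumptions tried. The size rests on R², the number of covariates and the trigger threshold, none of which the document gives. If the available covariates predict S100B only weakly, the gain is small and the remaining benefit is a primary result that is named in advance.

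**What to change.** Replace the trigger sentence with one named primary analysis of cord S100B: a linear regression on treatment plus a short list of prognostic covariates known at randomisation, fixed before unblinding and used whatever the observed balance. Candidates are centre and gestational age, and the basis of the distress diagnosis if it is recorded; the article does not say that it is. State that the same model is used at the interim and final analyses, so that the spending boundary applies to one defined statistic. Report the unadjusted and rank-based results as sensitivity analyses.

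Keep the mean-difference scale on which the trial is sized. A log scale would change the quantity being estimated, and should be used only if fixed in advance for a stated reason.

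The cost is a few sentences of text and the need to agree the covariate list before unblinding. No extra recruitment is needed. The gain cannot be promised, because it depends on how strongly the chosen covariates predict S100B.
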